#### 5.4 TNM stages and histological classification data check

In this study, the TNM stage and histological classification are based on UICC-7 and ICD-10, respectively. In this study, the pathological results of specimens resected after surgery will be used as histological classification data. A total of 3 subjects who refused surgery ( $n = 1$ ) and had inadequate medical examination data were deemed as missing.

#### 5.5 Breast density classification

In this study, we used cases enrolled from the screening center in Miyagi prefectures, as we could examine and confirm the breast density. Mammography density measure was evaluated depending on the fifth edition of Breast Imaging Reporting and Data System (BI-RADS), visual judgment data were classified as follows: (a) almost entirely fatty; (b) scattered areas of fibro-glandular density; (c) heterogeneously dense, which may obscure detection of small masses; and (d) extremely dense, which lowers the sensitivity of mammography screening.

Three expert physicians reevaluated mammographic density of the first screening. No personal identifiers were contained in the digital mammograms. All information of screening results, medical check and follow up data were blinded.

### 6. Analysis Methods

#### 6.1 Statistical analyses of the primary endpoints

This plan describes the analysis of the primary endpoints. Not only to compare between intervention and control group but from a different angle, focusing on breast density and ability of each modality.

The objectives of this study include;

1# To estimate and compare the sensitivity, specificity, screen-detected cancers and interval cancers of the study group and control group.

2# To compare the sensitivity, specificity, screen-detected cancers and interval cancers between dense and non-dense group.

3# To estimate sensitivity of each modality according to breast densities and study groups.

4# To estimate clinical stage and histological findings of screen-detected cancers and interval cancers according to breast density.

5# To estimate recall rate and biopsy rate of each modality according to study group.

## 6.2 Pooling data for analyses

First, the appropriateness of a pooled analysis in subjects who are randomized individually or by cluster will be examined.

In this analysis, study participants assigned by individual randomization and cluster randomization will be analyzed. Cluster randomization in the study will be as follows: Communities or healthcare providers are a randomization unit; explanation and consent are given individually; interventional effect is on an individual basis; and subjects with a diagnosis of breast cancer are those with objective data from a medical examination.

For the estimation of the primary endpoints, generalized estimating equation (GEE) with a compound symmetry structure as a working correlation matrix will be used. Analyses including only subjects who are randomized individually or by cluster will be performed, and it will be reviewed that the point estimates of the primary endpoints are similar. Furthermore, a model including the randomized groups as well as an interaction between the randomization methods (either individual or cluster) and randomized groups as an explanatory variable will be applied to subjects pooled from the two analyses, and it will be evaluated that the interaction effect is not statistically significant. If there is no interaction, a pooled analysis including subjects who are randomized individually and by cluster will be carried out.

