## 2.5 Sample size

### Primary endpoints:

The primary endpoints are defined as differences in sensitivity/ specificity and a detection rate of the first breast cancer screening between the intervention group and non-intervention group as previously mentioned. The sample size was calculated based on a previous study comparing sensitivity between screening with CBE alone and mammography in combination with CBE.

In this study that was used for understanding interval cancer (cancer identified in screened individuals without abnormality during a period between the screening and the next screening) in population-based cancer registry data in Miyagi Prefecture, the sensitivity of breast cancer screening using mammography in combination with CBE was superior to that of CBE alone in all age groups. However, the sensitivity was 71.4% for the age of 40 to 49 years, 85.8% for the age of 50 to 59 years, and 87.2% for the age of 60 to 69 years; thus, it was lowest for the 40's. Of 20,587 subjects aged 40 to 49 years, breast cancer occurred in 63 subjects during two years after screening including screen-detected breast cancer. Of these, screen-detected breast cancer was in 45 subjects, and interval cancer was in 18 subjects (sensitivity:  $45/63 = 71.4\%$ ).

Furthermore, assuming that a combination with ultrasonography would increase the number of subjects with screen-detected cancer and that the incidence of interval cancer would be decreased by half (decrease from 18 to 9

subjects), sensitivity in the ultrasonography combined group would be 86% (54/63). A total of 130 subjects with breast cancer would be necessary for demonstrating this increase in sensitivity with a two-sided significance level of 5% at a power of 80%. When it was converted to the number of subjects undergoing screening, a sample size of 42,500 subjects per group was estimated.

Secondary endpoint:

The secondary endpoint is defined as difference in the cumulative incidence rate of advanced breast cancer during the follow-up period between the intervention and non-intervention groups as previously mentioned. As with the primary endpoints, the sample size was calculated based on the previous study comparing sensitivity between screening with CBE alone and mammography in combination with CBE.

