|                                                                              | Mean, standard deviation, median | Significant digits will be rounded to the nearest tenth and displayed up to one digit.                                                                                                                                                                      |
|                                                                              | Minimum                          | The same number of figures as significant digits will be displayed.                                                                                                                                                                                         |
|                                                                              | Maximum                          | The same number of figures as significant digits will be displayed.                                                                                                                                                                                         |
|                                                                              | Interquartile range              | The same number of figures as significant digits will be displayed.                                                                                                                                                                                         |
| Test/ estimation                                                             | P value                          | Rules specified by a journal, to which results will be submitted, will be followed. The value will be rounded off to the nearest thousandth and displayed up to three decimal places. However, when it is less than 0.001, it will be displayed as < 0.001. |
|                                                                              | Significance level               | A two-sided test will be performed with a significance level of 5%. If other values are used for significance levels, they will be mentioned at each time. The confidence coefficient of interval estimation will be two-side 95%.                          |

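### SAP 6.2 gates the pooled primary analysis on a non-significant interaction from a model that names no randomisation-method main effect, so as worded it does not test effect homogeneity

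*Combined protocol and SAP*

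**What the plan says.** SAP 6.2 sets three steps before pooling.

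- The primary endpoints are estimated separately in individually and in cluster-randomised women, and the point estimates are reviewed for similarity. No criterion for similarity is given.
- A model is fitted to all women, described as "a model including the randomized groups as well as an interaction between the randomization methods (either individual or cluster) and randomized groups".
- The pooling rule follows: "it will be evaluated that the interaction effect is not statistically significant. If there is no interaction, a pooled analysis including" both sets of women is carried out.

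No separate level is set for this test, so the general rule of SAP Section 8 (two-sided, 5%) applies. SAP 7.2.2, the other description of the primary GEE, gives the robust variance and the compound-symmetry working correlation but lists no covariates. The primary endpoints (SAP 2.4.1) are sensitivity, specificity and detection rate. The trial was sized on sensitivity alone (SAP 2.5).

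**The concern.** A group-by-method interaction measures a difference in treatment effect only if both main effects are in the model. With 0/1 indicators and no method term, the two control strata share one intercept, and the interaction coefficient compares the ultrasound arm of one stratum with that of the other. With SAS CLASS coding and no method term, the model is saturated and the term becomes a 2-degree-of-freedom test of method within group. Neither is the intended question.

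Unequal baselines are plausible. Organisations join under one design or another (protocol Section 3), and facilities may or may not add clinical breast examination, equally in both groups (protocol 6.3). Control sensitivity could therefore differ by method even if ultrasound adds the same benefit everywhere.

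Even with the right model, the rule reads non-significance as no interaction. That needs a test with adequate power, and none is shown. The data then choose whether the pooled analysis is done. The plan does not say what is primary if the interaction is significant, or if the three endpoints disagree.

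**Working it through.** **Inputs from SAP 2.5.** Control sensitivity 45/63 = 71.4% ("Of these, screen-detected breast cancer was in 45 subjects, and interval cancer was in 18 subjects"); ultrasound-group sensitivity 54/63 = 85.7%; odds ratio (54/9)/(45/18) = 6.0/2.5 = 2.40; "A total of 130 subjects with breast cancer would be necessary"; cancer rate 63/20,587 ("Of 20,587 subjects aged 40 to 49 years, breast cancer occurred in 63 subjects during two years after screening").

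**Reproducing the plan's figure.** Two proportions, pooled variance, no continuity correction, mean 0.7857:

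n = [1.960 x sqrt(2 x 0.7857 x 0.2143) + 0.842 x sqrt(0.2041 + 0.1224)]^2 / 0.1429^2 = 129.

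The stated 130 therefore reproduces as a number per group, although the SAP calls it a total. Conversion: 130 x 20,587/63 = 42,481, stated as 42,500. The protocol target of 60,000 per group gives 60,000 x 63/20,587 = 184 cancers. I use 130 to 184 per group. The SAP 3.1 schedule (40,000 per group) gives 122, so slightly less power.

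**Assumptions not in the documents.** The share of cancers in clusters (10-50% for power, 20-50% for the simulations) and zero intracluster correlation, which favours power.

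**1. False rejection of the model as worded, 0/1 coding.** Let the odds ratio be 2.40 in both strata, but control sensitivity 60% in clusters. Ultrasound-arm odds are then 1.5 x 2.40 = 3.6 (78.3%) in clusters and 6.0 (85.7%) elsewhere. There is no true interaction, yet the tested coefficient is ln(3.6/6.0) = -0.511.

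With 130 per group and half in clusters: SE = sqrt[1/(65 x 0.1701) + 1/(65 x 0.1224)] = 0.465, z = 1.10, rejection about 20%. Over 130-184 cancers and 20-50% in clusters, simulation with robust standard errors gives:

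- as worded, 0/1 coding: about 17-25%;
- as worded, CLASS coding: about 24-43%;
- with the method main effect: about 4-6%.

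**2. Missed interaction, 0/1 coding.** Let the benefit be absent in clusters, with cluster control sensitivity already 85.7%. The ultrasound arms are equal, so the tested coefficient is zero. It is declared significant in about 2-4% of trials, against about 16-32% with the full model.

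**3. Power of the correct model, sensitivity.** Benefit present (2.40) in individually randomised women and absent in clusters, equal baselines, 130 per group, half in clusters:

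SE = sqrt[3/(65 x 0.2041) + 1/(65 x 0.1224)] = 0.593; z = ln(2.40)/0.593 = 0.875/0.593 = 1.48; power about 31%.

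| Cluster effect | 130 per group | 184 per group |
|---|---|---|
| Log odds ratio halved | 7-11% | 8-14% |
| Absent | 16-32% | 20-42% |
| Reversed | 50-85% | 65-95% |

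Ranges cover 10-50% of cancers in clusters. For 80% power against an absent effect, about 470 (50% in clusters) to 670 (20%) cancers per group are needed, or about 153,000 to 219,000 women.

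**4. Other endpoints.** Detection rate, with the gain from 45 to 54 per 20,587 absent in clusters and 50,000 per group: 7-11% power. Specificity has no value in the documents. Assuming 91% or 95% in controls and 40,000 per group, power is 78-100% for a 2-3 point loss confined to one stratum.

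**The case against.** **The omission may be shorthand.** The SAP says what the model includes, not that method is left out, and the text may be a translation. A reader might infer that the sponsor chose to exclude the main effect; the documents do not show that. What stands is that the model deciding on pooling is not written out, and no other section completes it. That the final pooled GEE omits method is likewise only an inference from silence in SAP 7.2.2.

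**Coding matters.** A reader might infer that control women are always forced to a common sensitivity. That holds for 0/1 indicators, not for CLASS coding, and no coding is stated. The near-zero detection in step 2 also belongs to 0/1 coding. False alarms persist under CLASS coding.

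**The missing term does not cause the low power.** With equal baselines and the benefit absent in clusters, the model as worded rejects in 39-65% of trials, against 23-42% for the full model. The small number of cancers is the cause. Nor is power low throughout: specificity is well powered under the assumed values, and so, in most settings, is a full reversal on sensitivity.

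**Near-certain false alarms on specificity** might also be inferred from the large numbers of women. Such figures need a specificity, a stratum split and an intracluster correlation that the documents do not give, and they fall with other coding or with clustering.

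**Safeguards exist.** Stratum estimates are reviewed first, and SAP Section 10 refers unspecified data handling to the committees. But the review has no criterion, and referral after the result is known is not prespecification.

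**Scope.** Protocol Section 18 says the primary analysis has been reported, and this SAP version serves the density study in Miyagi women (SAP Sections 1 and 5.5). Whether both methods occur there is unstated; if not, the test has no role in that analysis.

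**Conclusion.** The concern holds in a limited form. As worded, the pooling test does not address whether the ultrasound effect differs by randomisation method, and a baseline difference can trigger it: about 17-25% false rejection on sensitivity with 0/1 coding, against about 4-6% with the main effect, under the assumptions in step 1. If the main effect was intended, this part is a defect of wording only.

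The second part stands either way. With about 16-42% power on sensitivity against a benefit wholly absent in clusters, and 7-11% on detection rate, a non-significant result cannot be read as no interaction. Any intracluster correlation would lower these figures further. This does not extend to specificity under plausible assumed values. The lack of a similarity criterion and of a named primary analysis after a significant result also stands. Nothing here shows that pooling was wrong or that the ultrasound effect differs between methods.

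**What to change.** In SAP 6.2:

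- Write the interaction model as group + method + group x method, and state the coding.
- Include the method main effect in the pooled GEE, and say so in 7.2.2.
- For each primary endpoint, report the method-specific estimates and the interaction with its 95% CI, as description.
- Make the pooled, method-adjusted GEE primary regardless of the interaction p-value. Alternatively, prespecify a tolerance for the difference in effect and the action if it is exceeded, including when endpoints disagree.
- State whether both randomisation methods are present in the data analysed under this version.

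The cost is SAP wording and one model term, to the extent that both methods are present. No new data are needed.

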## 6.3 Analysis set

Efficacy analyses will be performed in the intention-to-treat (ITT) set. The ITT set will be a set of participants enrolled in the study excluding (1) non-randomized enrolled subjects, (2) ineligible subjects, (3) subjects withdrawn consent, (4) double-entry subjects, and (5) subjects without data that should be analyzed for demonstrating efficacy (subjects without first screening data).

After all input, correction and sending functions of EDC for study data at the study site are locked, logical check and inquiries to applicable study sites will be made based on data received by the EDC system at the central data center. The final review of the concerned subjects will be carried out based on confirmation, responses and reports from the study sites and source documents.

## 6.4 Preparation of SAS data set for analysis (Data Source)

When preparing an analysis data set, the below-mentioned verification should be conducted.

### 6.4.1 Verification of compliance with randomization

After the EDC input function at the site is locked, the key will be opened. System numbers issued by the central randomization and the randomized groups, and system numbers inputted in the EDC at the site and the randomized groups will be cross-checked using data received by the EDC system at the central data center, and inquiries on the following items should be made to each study site:

- (1) Verification of subjects incompliant with randomization who underwent screening different from that centrally randomized.
- (2) Verification of a system number that a number issued by central randomization is not entered in the EDC.
- (3) Verification of subjects for whom numbers different from those assigned by the central data center are inputted in the EDC.

- (4) Verification of a system number that has been entered once but deleted.
- (5) Double entry
- (6) Subjects whose date of consent for the study participation is after the date of screening.

#### 6.4.2 Subjects not meeting the eligible criteria

##### (1) History of breast cancer

When it is confirmed that there is no difference between EDC input data and source documents entered by the participants, the subjects should be excluded from the analysis.

##### (2) Other cancers within 5 years

When it is confirmed that there is no difference between EDC input data and source documents entered by the participants, the subjects should be excluded from the analysis.

##### (3) Age

This study was conducted mainly on the basis of resident screening and occupational screening by local municipalities. For the standard age qualifying breast cancer screening in Japan, age reached in the Year or age at last birthday was used so that the age of  $40 \pm 2$  -  $50 \pm 2$  years would be analyzed.

#### 6.4.3 Withdrawal of consent

Subjects who completely withdraw consent (when cross-checking with external data is refused) will be excluded from the analysis.

#### 6.4.4 Deviation

##### (1) Subjects without first screening data

For subjects whose participation/ enrollment is recorded but first screening data are not inputted, in accordance with the Section <5.2.1 Full Analysis Set> of the ICH Guideline “Statistical Principles for Clinical Trials,” subjects without data at the time of intervention (i.e., without first screening data) should be deemed as meeting exclusion from the ITT analysis as well thus will be excluded from the analyses of sensitivity and specificity of the first screening.

##### (2) Subjects with inadequate test (deviation)

- i. Subjects in the intervention group who have no ultrasonographic data.
- ii. Subjects in the non-intervention group whose ultrasonographic data are inputted.

## 7. Statistical Analyses

### 7.1 Comparison of characteristics of baseline demographic variables and the distributions of baseline factors

Baseline demographic variables will be age at the time of enrollment, history of breast cancer screening (presence or absence, date of screening and methods), the age of first menstruation, menstruation status, number of pregnancies, frequency of childbearing, age at the first delivery, feeding history, family history of breast cancer, history of breast surgery, and history of mammary gland disease.

351 Age at the time of enrollment and time (month) from the previous screening. History of screening, menstruation  
 352 status, feeding history, family history, history of breast surgery, and history of mammary gland disease. Time  
 353 (month) from the previous screening, which is a continuous variable, will be categorized. The age of first  
 354 menstruation, number of pregnancies, frequency of childbearing, age at the first delivery, and number of  
 355 first-degree relatives with breast cancer will be categorized in accordance with the Gail model for performing an  
 356 international comparison.

357 For characteristics of baseline demographic variables, descriptive statistics will be calculated to describe the data.  
 358 Continuous variables will be summarized with a number, mean, standard deviation, range and mode. Categorical  
 359 data will be presented as percentages. For methods of comparisons of the distributions of baseline factors,  
 360 differences in categorical data will be assessed by Fisher’s exact test and the Chi-square test, and differences in  
 361 continuous data by the Mann-Whitney’s U-test. All tests will be two-sided.

362 7.2 Analyses of a detection rate, sensitivity and specificity of the first screening and calculation methods  
 363 for 95% confidence intervals (CIs)

364 7.2.1 Definitions and calculation formulas

Table 2. Definitions and calculation formulas of a detection rate, sensitivity and specificity of the first screening

|                                            |                                                                                                              |                                                                              |
|--------------------------------------------|--------------------------------------------------------------------------------------------------------------|------------------------------------------------------------------------------|
| Detection rate of screening, %
(95% CI) | The number of cancers with a positive initial interpretation among 1,000 screening examinations.             |                                                                              |
| Sensitivity, %
(95% CI)                 | $\text{Sensitivity} = \frac{[5]\text{TP}+[7]\text{TP}}{[5]\text{TP}+[7]\text{TP}+[1]\text{FN}+[3]\text{FN}}$ | (Number of true positive assessments) / (Number of all positive assessments) |
| Specificity, %
(95% CI)                 | $\text{Specificity} = \frac{\text{TN}}{\text{TN}+\text{FP}}$                                                 | (Number of true negative assessments) / (Number of all negative assessments) |

365 The 95% CIs will be calculated using the binomial distribution method.

366 At the statistical analysis/ data monitoring committee meeting held on October 28, 2013, consensus was reached  
 367 that subjects having an unknown status would be excluded from the analyses of sensitivity and specificity.

368 7.2.2 Method of the primary analysis taking account of correlations within the cluster

369 All “screen-detected cancer,” “interval cancer” and “subjects without cancer” at the first screening to be used for  
 370 calculating sensitivity/ specificity, the primary endpoints, are binary outcomes. As an analysis method for  
 371 estimating the primary endpoints in the two groups, GEE taking account of correlations within the cluster will be  
 372 used. For estimation of the parameters, robust variance estimator with a compound symmetry structure as a  
 373 working correlation matrix will be employed.

374

375     **8. Statistical Analysis Rules**

| Item                                                                         |                                  | Display digit                                                                                                                                                                                                                                               |
|------------------------------------------------------------------------------|----------------------------------|-------------------------------------------------------------------------------------------------------------------------------------------------------------------------------------------------------------------------------------------------------------|
| Subject background characteristics, sensitivity, specificity, detection rate | No. of subjects                  | To be displayed as integers.                                                                                                                                                                                                                                |
|                                                                              | Proportion (percentage)          | To be rounded to the nearest tenth and displayed up to one digit.                                                                                                                                                                                           |
|                                                                              | 95% CI for the rate (percentage) |                                                                                                                                                                                                                                                             |
|                                                                              | Detection                        | To be displayed as %                                                                                                                                                                                                                                        |
| Descriptive statistics                                                       | No. of subjects                  | To be displayed as integers.                                                                                                                                                                                                                                |
|                                                                              | Mean, standard deviation, median | Significant digits will be rounded to the nearest tenth and displayed up to one digit.                                                                                                                                                                      |
|                                                                              | Minimum                          | The same number of figures as significant digits will be displayed.                                                                                                                                                                                         |
|                                                                              | Maximum                          | The same number of figures as significant digits will be displayed.                                                                                                                                                                                         |
|                                                                              | Interquartile range              | The same number of figures as significant digits will be displayed.                                                                                                                                                                                         |
| Test/ estimation                                                             | P value                          | Rules specified by a journal, to which results will be submitted, will be followed. The value will be rounded off to the nearest thousandth and displayed up to three decimal places. However, when it is less than 0.001, it will be displayed as < 0.001. |
|                                                                              | Significance level               | A two-sided test will be performed with a significance level of 5%. If other values are used for significance levels, they will be mentioned at each time. The confidence coefficient of interval estimation will be two-side 95%.                          |
|                                                                              | CI                               | Significant digits will be rounded to the nearest tenth and displayed up to one digit.                                                                                                                                                                      |

376     **9. Technical Matters**

377     For all analyses, SAS® software, Version 9.4 (SAS Institute Inc., Cary, NC) will be used.

378     **10. Validation of Analysis Results**

379     For the statistical analyses in this study, under the supervision of both statistical analysis/ data monitoring  
380 committees, data sets and SAS programs to be applied to the statistical analyses will be prepared, and analysis  
381 operations will be carried out. If data handling is not specified in the analysis plan or other relevant documents, a  
382 request for decision and consultation should be, as necessary, made to the statistical analysis/ data monitoring  
383 committees, and data should be processed upon consensus.

384     The validity of the analysis SAS program should be ensured by review, preparation, execution, validation and  
385 verification of an SAS program for each analysis using double programming. Practical analysis operations will be  
386 performed by two staffs. One has experience with SAS for 14 years (Tohoku University, [name] M.D.,  
387 Ph.D., CCRP® (Certification of Clinical Research Professionals by SoCRA), and the other has experience with SAS  
388 for 21 years (J-CRSU, [name], SAS Certified with SAS Base Programmer for SAS®9).

389 In the program verification and validation, the following items should be checked that: (1) data are the latest; (2)  
390 the program to be executed is the latest; (3) if multiple programs are involved, the order of the analysis is correct;  
391 (4) date of execution; (5) no error or warning is displayed on the SAS log in the course of execution; and (6)  
392 numerical values in a report prepared as output results are consistent.

393 The analysis plan should be implemented upon confirmation with Professor, [name] (Tohoku  
394 University) and Professor, [name] (Tohoku University). Specific instructions and consultations on the  
395 analysis methods should be requested to Professor, [name] (the University of Tokyo/ Chuo University/  
396 J-CRSU), Professor, [name] (Tohoku University), Professor, [name] (Osaka University), and  
397 [name]. (National Cancer Center). For verification of medical and clinical meaning of data  
398 classification, directions should be sought from Professor, [name], (Tohoku University) and Professor,  
399 [name], (Tohoku Medical and Pharmaceutical University).

400 **11. Changes to Planned Analyses**

401 At a statistical analysis/ data monitoring committee meeting held on January 27, 2014, it was decided to exclude  
402 non-randomized subjects from the analyses of the primary endpoints.

403 **12. List of the Statistical Analysis Committee Members**

|     |                      |                                                                                         |
|-----|----------------------|-----------------------------------------------------------------------------------------|
| 404 | © [name]  | Professor, International Research Institute of Disaster Science, Department of Disaster |
| 405 |                      | Public Health, Graduate School of Medicine, Tohoku University                           |
| 406 | [name]          | Executive Director/ Vice President, Department of Public Health, Yamagata University    |
| 407 |                      | Faculty of Medicine                                                                     |
| 408 | [name]      | Director, Cancer Detection Center, Miyagi Cancer Society                                |
| 409 | [name]         | Professor, Department of Biostatistics, School of Public Health, Graduate School of     |
| 410 |                      | Medicine, the University of Tokyo                                                       |
| 411 | [name]   | Director, Public Health Policy Research Division, Research Center for Cancer            |
| 412 |                      | Prevention and Screening, National Cancer Center                                        |
| 413 | [name]   | Professor, Division of Biostatistics, Graduate School of Medicine, Tohoku University    |
| 414 | [name]      | Researcher, Department of Breast and Endocrine Surgical Oncology, Graduate School       |
| 415 |                      | of Medicine, Tohoku University                                                          |
